#### Primary outcome: SM symptoms

2.3.1

*SCED*: For purpose of this study, the research team collaborated with experienced SM therapists and an expert on SCED in clinical settings to design a short 9-item questionnaire that is used as a frequent measurement for the SCED (see Appendices A and B). The questions on this frequent measure are assessed on a 5-point Likert scale. Parents and teachers are asked to report on the communicative and speaking behavior of the child in each specific week, three times a week (Monday, Wednesday and Friday) through a smartphone application, resulting in at least 117 time points.

*Clinical and standardized assessment*: Both parents fill out the Dutch translation of the Selective Mutism Questionnaire (SMQ-NL). The questionnaire contains 16 questions that are scored on a four-point Likert scale. The SMQ-NL has high reliability and good validity [31]. Teachers are asked to report on the Social Context of Speaking (SCS, see Appendix C).

#### Secondary outcomes

2.3.2

*Emotional and behavioral problems:* will be assessed using the pre-school (ages 1,5–5) and school-aged (ages 6–18) versions of the Child Behavior Checklist (CBCL) and the Teacher Report Form (TRF) of the Achenbach System of Empirically Based Assessment (ASEBA). Both measures have a high reliability and validity [32,33].

*Anxiety*: The Dutch translation of the Fear Survey Schedule for Children Revised (FSSCR) will be used to measure symptoms of fear. The questionnaire measures the level of fear related symptoms and phobias in children across five different domains. The questionnaire has adequate reliability and validity [34].

*Psychiatric comorbidity*: the Structured Clinical Interview for DSM-5 disorder in children and adolescents (SCID-junior) will be administered. The SCID-junior is a reliable and valid instrument for the classification of DSM-5 disorders in children and adolescents [35].

*Parenting burden questionnaire*: the Dutch Parenting Stress Questionnaire will be filled out by parents (in Dutch translated as *Opvoedingsbelasting vragenlijst; OBVL)*. The OBVL contains five subscales and a total score. The OBVL has good reliability and adequate validity [36].

*Severity of psychopathology*: The Clinical Global Impression Scale (CGI) is a valid and reliable measure of severity of psychopathology across time [37]. The CGI has good validity and reliability estimates differ across populations [37].

*Family accommodation*: The Dutch translation of the Family Accommodation Scale – Anxiety (FASA) [38]. The FASA is a reliable and valid instrument for assessing family accommodation of childhood anxiety [39]. The FASA has also been validated for the Dutch population [40].

*VRET evaluation*: The time participants spent practicing the exercises will be monitored through the web interface which is used by the remote supervisor to control the virtual environment. The psychologist-researcher will plan a semi-structured interview with parents to document experiences of the VRET-and to ensure proper usage of the application. At the end of the study, parents and children are asked to share their experiences in a short interview.

After each session the following questionnaires will be filled out:

*Overall well-being*: The Childhood Outcome Rating Scale (CORS) will be used to track progress and well-being over the course of the treatment. After each session the therapist asks the child to report on four questions using a visual analogue scale. The CORS is a well-balanced self report measure between reliability and validity compared to longer measures [41].

*Anxiety*: Children are asked to rate their anxiety after each therapy session and VR session at home using the Visual Facial Anxiety Scale (VFAS) [42]. The VFAS is a valid measure of state anxiety.

#### Covariates and predictors

2.3.3

*Parental behavioral and emotional problems*: Both parents are asked to complete the Adult Self-Report (ASR) to assess parental psychopathology. The ASR is an extension of the ASEBA scales CBCL and TRF. It provides a total score and scores for an internalizing and externalizing subscale. The Dutch self-report version has been proven to be a valid and reliable instrument to measure adult problem behavior [43].

*Parenting behavior*: The Parental Attitude and Behavior Index (PABI) consists of 20 scales that can be classified into three adaptive domains (warmth, structure and autonomy) and three maladaptive domains (hostility, control and overprotection). The PABI has demonstrated good reliability and validity [44].

*Immersive tendencies*: The Immersive Tendencies Questionnaire [45] is a valid and reliable instrument to assess immersion The questions were rephrased in such a way that parents can evaluate the immersive tendencies of their child.

*Communication*: The Vineland-3-NL will be used to assess adaptive functioning in the domain of communication and the subdomains receptive-, expressive- and written communication. The Vineland-3-NL is a valid and reliable instrument [46].

## Statistical analyses

3

### Sample size calculation

3.1

To establish the efficacy of a treatment, SCEDs involve the comparison of different treatment phases. For statistical analysis, each phase of the intervention needs at least five to 20 datapoints [34]. The study design has five phases, and it is ensured that each phase of the intervention will have at least five data points. SCED methodology provides substantial within-person statistical power due to the high number of repeated measurements per participant, ensuring that each individual case has sufficient data to detect meaningful within-person changes.

A power analysis was conducted using the Shiny app SCED Power Analysis [47]. A meta-analysis evaluating the efficacy of CBT for SM reported a large effect size (Hedges' adjusted g = 1.00 [0.62–1.39]) [48]. To detect an expected effect size of Cohen's d = 0.8 and an autocorrelation of 0.4, a sample size ranging from four to eight participants should provide sufficient power to establish an effect from baseline to intervention using the Permutation Distance Test [49]. The planned power analysis pertains to the aggregated, group-level effect, which will be estimated through a meta-analytic synthesis of the individual SCED p-values. The target sample size of *N* = 15 participants refers to the number of individual cases contributing to the pooled group effect.

Given that SM often occurs in young children the physical comfort of the headset might be compromised for children with smaller head sizes. To account for potentially higher dropout rates and missing data, our aim is to include 15 participants to ensure sufficient data for analysis.

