
## Design and methods

2

**Study Design:** This study is a single-case experimental design (SCED) carried out in a specialized academic center for child and adolescent psychiatry (Levvel, Amsterdam, The Netherlands). In a SCED, statistical power is generated through frequent and repeated measurements of the primary outcome over time to monitor within-subject changes [22]. This makes a SCED highly suitable for measuring the treatment effect of individualized treatments (such as children with SM). Due to their adaptability and statistical rigor, SCEDs can be used for innovative treatments in order to generate initial evidence before moving on to more traditional group-based designs [22,23]. This study employs a five-phase design: baseline (A: 2 weeks, no treatment), three individualized treatment phases. The first treatment phase (B: protocol step 1–5, treatment) requires the child to respond to the teacher by producing sounds. Treatment phase two requires the child to respond verbally to teacher (C: protocol step 6–10, treatment). During the last phase of the treatment focuses on the intensification of verbal communication to solidify treatment gains (D: training phase, treatment) and follow-up phase (E: 12 weeks, no treatment). Previous research in our center concluded that the average treatment duration is on average 25 weeks (see Fig. 1).

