**Fig. 1 fig1:**
[figure not shown]
Study design.

Experience sampling method (ESM) assessments (see Paragraph 2.3.1 and Appendices A and B) are used to quantify SM symptoms. These assessments are conducted thrice weekly via the M-path smartphone application [24] by parents and teachers. Considering the average treatment length of 25 weeks, yielding approximately 117 time points across all phases. To ensure adherence and feasibility, the study design was developed balancing a valid number of frequent assessments (after consulting a statistics expert, SB) with the burden for participants, based on ample experience of our research group in conducting ESM studies.

ESM measures are supplemented by comprehensive assessments at key time points. The comprehensive assessment consists of a standardized diagnostic measure of the primary outcome (i.e. SM symptoms), secondary outcomes (i.e. emotional and behavioral problems, anxiety, parenting burden, family accommodation and VR evaluation) as well as relevant predictors, covariates, and potential confounding factors (i.e. parental behavioral and emotional problems, parenting style, immersive tendencies and communication). Fig. 1 provides an overview of the study procedures and assessments conducted at each time point.

The baseline assessment [T0] includes both primary and secondary outcomes, and potential confounding factors, as reported by parents, teachers, and children. At the start of each study phase [T1], [T2], and [T3] parents and teachers report on the *primary outcome* only. Post-treatment [T4] and follow-up [T5] assessments are similar to the baseline assessment, measuring only the primary and secondary outcomes across all informants. Due to the individualized treatment approach, clinical assessments are standardized by therapeutic progress rather than chronological time, resulting in variable intervals between assessments across participants.

**Inclusion criteria:** Children are eligible if they attend primary school, are 4–13 years old, and are referred to our center for diagnosis and treatment for SM between January 2025 until December 2026. Psychiatric comorbidity is permitted, as long as SM is the primary treatment target. Medication use is allowed, provided it has been stable for four weeks prior to participation and remains unchanged throughout treatment.

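### The sample-size section claims adequate power for each individual child, but at the plan's own effect size and autocorrelation a six-report baseline gives only about 24–27% two-sided power per child

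*Protocol article*

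**What the plan says.** Section 3.1 (Sample size calculation) makes two statements about power.

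- **Individual level.** Repeated measurement is said to give substantial within-person power, "ensuring that each individual case has sufficient data to detect meaningful within-person changes". No effect size, alpha or power figure is attached to this.
- **Group level.** With "an expected effect size of Cohen's d = 0.8 and an autocorrelation of 0.4", four to eight participants are said to suffice for a baseline-to-intervention effect using the Permutation Distance Test (PDT). The section then says that this analysis concerns the aggregated effect, obtained by combining the individual p-values, and that the target of 15 counts the cases contributing to it.

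The same section states that "it is ensured that each phase of the intervention will have at least five data points".

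Section 2 fixes the amount of data. The first phase is "baseline (A: 2 weeks, no treatment", the last is "follow-up phase (E: 12 weeks, no treatment", and on reporting: "These assessments are conducted thrice weekly via the M-path smartphone application". The total is given as: "Considering the average treatment length of 25 weeks, yielding approximately 117 time points across all phases".

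Section 3.1.1 applies the PDT between phases within each child on the primary outcome, alongside visual analysis and Tau-U. A reliable change index on the SMQ and the SCS serves as validation.

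**The concern.** The per-case sentence rests on the total number of reports, about 117 per child. A comparison of two phases is limited by the shorter one, and the baseline is very short. Six positively correlated reports carry less information than six independent ones, and a long treatment phase cannot make up for that. The group calculation does not carry over to one child, because it draws its power from several children.

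This matters because a child-level test on the primary outcome is planned, and section 4 justifies the design by what it shows about response in the individual. A reader who trusts the sentence would give a non-significant child-level result more weight than it can bear.

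**Working it through.** **Inputs**

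- d = 0.8 and lag-1 autocorrelation ρ = 0.4 (section 3.1).
- Baseline: 2 weeks × 3 reports = 6 per informant (section 2).
- Treatment: 25 weeks × 3 = 75 reports on average. An equal split over phases B, C and D gives 25 each; the equal split is my assumption.
- Follow-up: 12 weeks × 3 = 36.
- Alpha and sidedness are not stated. I assume 5% and show both two-sided and one-sided results.

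**The plan's own figures first**

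- Reports: 3 × (2 + 25 + 12) = 117, as stated.
- Participants: if the child-level results are combined by Stouffer's method, 80% pooled power is reached at 4 children (one-sided) or 5 (two-sided). Fisher's method on two-sided p-values needs about 9–10. The stated four to eight is recovered to within two children. The article does not name the combination method, so I put forward no single pooled power figure.

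**Per-child power**

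For a stationary AR(1) series with within-phase SD 1, the variance of a phase mean is

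Var(mean of n) = [1 + 2 Σ (1 − k/n) ρ^k] / n, summed over k = 1 to n − 1.

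For n = 6 the sum is 0.3333 + 0.1067 + 0.0320 + 0.0085 + 0.0017 = 0.4822, so the variance is (1 + 0.9645)/6 = 0.327. Six independent reports would give 0.167.

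The variance of the phase difference is Var(A) + Var(B) − 2 Cov(A, B). Power is Φ(d/SE − 1.96) two-sided and Φ(d/SE − 1.645) one-sided.

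- **6 vs 25:** 0.3274 + 0.0898 − 2(0.0074) = 0.402; SE 0.634; 0.8/0.634 = 1.26. Power 24% two-sided, 35% one-sided.
- **6 vs 75:** 0.3274 + 0.0307 − 2(0.0025) = 0.353; SE 0.594; 0.8/0.594 = 1.35. Power 27% two-sided, 38% one-sided.
- **6 vs an effectively unlimited treatment series:** SE 0.573; 0.8/0.573 = 1.40. Power about 29% two-sided.
- **5 vs 5 (stated minimum):** 0.3787 + 0.3787 − 2(0.0435) = 0.670; SE 0.819; 0.8/0.819 = 0.98. Power about 16% two-sided, 25% one-sided.

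The third line shows that the baseline is the limit: no number of treatment reports takes two-sided power above about 29%.

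**Effect needed for 80% two-sided power:** (1.96 + 0.84) × SE, which is 1.78 for 6 vs 25 and 1.67 for 6 vs 75.

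**Contrasts that do not involve the baseline:** 25 vs 25 has SE 0.420 and 48% two-sided power (60% one-sided). 25 vs 36 has SE 0.388 and 54% (66% one-sided).

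**Sensitivity**

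- Simulated differences in medians, with critical values from the true autocorrelated null, give 22% (6 vs 25) and 25% (6 vs 75) two-sided, and 32% and 35% one-sided.
- Zero autocorrelation gives 42–47% two-sided, 55–60% one-sided.
- d = 1.0, the point estimate from the cited meta-analysis, gives 35–39% two-sided with ρ = 0.4.
- d = 1.39, the upper limit of its interval, gives 65% two-sided and 76% one-sided for 6 vs 75.
- If d is scaled on the innovation SD instead of the within-phase SD, power falls to 21–23% two-sided.

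The power app's own PDT code was not available, so these figures are for tests of phase means or medians that respect the autocorrelation.

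**Five points per phase**

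Six scheduled baseline reports leave room for one missed report per informant before the count falls below five. Phases B to D end on the child's progress, and the article states no minimum length for them.

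**The case against.** The best defence is that the sentence never says what a meaningful change is. A child who moves from silence to regular speech in class may well change by more than d = 1.7, and a change that large would be detectable. Section 3.1 also ties its power analysis openly to the group effect, so the per-case sentence can be read as a general remark about single-case designs. The first part stands as a limit on the point: very large changes are within reach. It does not rescue the sentence, because d = 0.8 is the effect the plan itself expects and section 3.1.1 tests each child.

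Alpha and sidedness are not stated, and the 24–27% applies only to two-sided contrasts with baseline. That is correct, and is why a range is given. A permutation test that ignored the autocorrelation would reject more often, about 37–51% two-sided, but its type I error would be about 13–19%, so that is not usable power.

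Three stronger readings are tempting, and the documents do not support them.

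- *The sample size is wrong.* It is not: 117 reports and four to eight participants are both recovered.
- *Children will be labelled non-responders.* No section classifies children by PDT p-value. Individual reading starts from visual analysis and adds Tau-U, with the reliable change index as a check, and section 3.1.3 uses the predictors only descriptively. Over-reading a null result is a risk for the reader and is not a planned rule.
- *A known share of children will fall below five baseline reports.* The article gives no response rates, and section 3.1.4 plans within-person imputation for the inferential analyses, so no count can be derived.

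**Conclusion.** The point holds for one sentence. The claim of sufficient data in each individual case has no supporting calculation and does not fit the plan's own inputs. At d = 0.8 and autocorrelation 0.4, with a 5% test assumed, no contrast examined reaches 80% power for one child, and under these assumptions roughly three in four children with a true baseline-to-treatment change of that size would be non-significant on a two-sided test. The result rests on d being scaled to the within-phase SD, on informants being analysed separately (pooling parent and teacher reports is not described), and, for the 25-report figures, on equal treatment phases.

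This is an unsupported statement of power, not an error in a printed number. The group-level analysis, the target of 15 and the primary outcome are unaffected, so it calls for a correction of wording rather than a change of design.

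**What to change.** In section 3.1:

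1. Withdraw the per-case sentence, or limit it to the pooled effect.
2. State per-child power as a range with its assumptions: for contrasts with baseline at d = 0.8 and autocorrelation 0.4, about 24–27% two-sided or 35–38% one-sided at 5%, and about 16% or 25% at five reports per phase. Give the alpha and sidedness actually intended.
3. State that a non-significant child-level PDT is inconclusive and is not evidence of no response.
4. Describe at least five points per phase as scheduled instead of ensured.

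The cost is wording, and a less favourable stated individual-level power. Sample size, visit schedule and planned analyses stay as they are.

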#### Primary outcomes

3.1.1

*SCED*: The ESM measure of SM symptoms is used to evaluate the primary outcome. In Single-Case Experimental Designs (SCEDs), visual analysis is the preferred starting point for assessing treatment effects. The ESM data are presented graphically to assess patterns in trend, level, and stability across and within intervention phases [50]. Additionally Tau-U will be reported [51]. Tau-U is a non-parametric effect size that was created for SCEDs reflecting the degree of non-overlap of observations between two phases. By incorporating both level changes and trend adjustments it is possible to control for baseline trends. Tau-U can be used for statistical testing and for meta-analytic purposes to establish a group effect of the intervention [51].

The Permutation Distance Test (PDT) [49] will be used to test the difference in medians between phases within an individual. The PDT tests the null hypothesis that the medians of the different phases are the same, while accounting for autocorrelation of the data.

*Standardized assessment:* To evaluate whether the change in the frequent assessment SM symptoms is reliable across the different study phases, a reliable change index (RCI) [52] will be computed for the SMQ and the Social Context of Speaking questionnaire. These questionnaires serve to validate the results obtained from the frequent measurements. To test for differences on a group level Friedman's analysis of variance (ANOVA) [53] will be used.

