### Assessments

2.3

Parents and teachers report on the ESM measures using the M-path smartphone application three times a week (Monday, Wednesday and Friday) for the entire study duration.

Supplementary clinical and standardized assessments will be administered online. Both parents are invited to fill out the questionnaires. If it is not feasible for both parents to participate, the parent who spends the most time with the child will be asked to complete the questionnaires. At baseline [T0], a comprehensive clinical assessment will be conducted to evaluate the primary study outcome, as well as relevant predictors, covariates, and potential confounding factors (see Table 2, for an overview). At the start of each new study phase [T1, T2, and T3], parents and teachers will report only on SM symptoms. At post-treatment [T4] and follow-up [T5], parents and teachers will report on both SM symptoms and confounding factors. A clinical interview with parents will be conducted during the pre-treatment, post-treatment, and follow-up assessments.

**Table 2 tbl2:** Overview of assessments and informants.

Instrument	Variable	Moment of assessment					
		T0	T1	T2	T3	T4	T5
*Primary outcomes*							
Selective Mutism Questionnaire (SMQ-NL)	SM symptoms	P	P	P	P	P	P
Social Context of Speaking (SCS)	SM symptoms	T	T	T	T	T	T

*Secondary outcomes*							
Child Behavior Checklist (CBCL)	Behavioral and emotional problems	P				P	P
Teacher Report Form (TRF)	Behavioral and emotional problems	T				T	T
Structured Clinical Interview for DSM-5 disorders in children and adolescents (SCID-5 Junior)	DSM-5 classification of disorders	P				P^a^	P^a^
Fear Survey Schedule for Children Revised (FSSCR)	Anxiety symptoms	C				C	C
Parenting Burden Questionnaire (Opvoedingsbelangsting vragenlijst: OBVL)	Parenting burden	P				P	P
Clinical Global Impression Scale – Improvement	Severity of psychopathology		Th	Th	Th		
Child Observation Rating Scale	Overall Well-Being		C	C	C		
Visual Facial Anxiety Scale (VFAS)	Level of Anxiety		C	C	C		
Family Accommodation Scale (FASA)	Family accommodation	P				P	P
Virtual reality evaluation	Evaluation of VR		P	P	P	P	

*Predictors*							
Adult Self Report (ASR)	Adult problem behavior	P					
PABI	Parenting style	P					
Immersive tendencies – Parent version	Immersive tendencies	P					
Vineland-3-NL for parents	Adaptive functioning	P					
Vineland-3-NL for teachers	Adaptive functioning	T					
Demographic variables	Demographics	P					

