#### Secondary outcomes

3.1.2

*Standardized assessment:* Overall well-being (CORS) and severity of psychopathology (CGI) will be plotted against time and will be subjected to visual inspection for upward and downward patterns. A Kendall's Tau correlation [54] will computed to evaluate whether there is a significant upward or downward trend in overall well-being or CGI scores during treatment.

The secondary outcomes changes in symptoms of anxiety (FSSCR), and psychological functioning (CBCL, TRF) between the baseline assessment, post-intervention assessment and follow-up assessment will be subjected to formal testing. These secondary outcomes are selected because they provide theoretically relevant validation and interpretation of the primary outcome measure. These outcomes will be evaluated by calculating an RCI. Friedman's ANOVA will be used to test for differences on a group level. Due to the risk of increased Type I error, appropriate correction methods for multiple comparisons where relevant (e.g., Benjamini–Hochberg) will be applied.

The remaining secondary measures, parenting burden (OBVL) and family accommodation (FASA), will be analyzed descriptively and treated as exploratory as these outcomes help to better understand the family system and how these factors may be associated with potential treatment effects. This approach allows us to maintain rigor in the interpretation of the primary endpoints, while using the secondary outcomes mainly to contextualize, validate, and deepen the understanding of the primary effects.

*Qualitative interview:* The qualitative data from the VR user experience evaluation will be examined using deductive thematic analysis to uncover and interpret key themes [55]. Qualitative interviews will complement the quantitative measures by providing insight into treatment acceptability and user experiences. These findings will help contextualize the quantitative outcomes and contribute to evaluating the feasibility of the intervention and the perceived role of VRET within the broader treatment. Feedback on the VRET application will also be collected to guide future improvements.

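### Section 3.1.1 and Table 2 disagree on which measure is primary, and the primary analysis has several possible tests with no stated error control

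*Protocol article*

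**What the plan says.** All references are to the protocol article.

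- **Section 3.1.1, diary.** The lead role goes to the experience-sampling diary: "The ESM measure of SM symptoms is used to evaluate the primary outcome". The analysis is visual inspection, Tau-U and the PDT, which "will be used to test the difference in medians between phases within an individual".
- **Section 3.1.1, questionnaires.** Of the SMQ and SCS it says: "These questionnaires serve to validate the results obtained from the frequent measurements". The same paragraph, still under the primary-outcomes heading, adds a group test: "To test for differences on a group level Friedman's analysis of variance (ANOVA").
- **Table 2 (section 2.3).** The block headed as primary outcomes has two rows, "Selective Mutism Questionnaire (SMQ-NL") from parents and "Social Context of Speaking (SCS") from teachers. The diary is not in the table.
- **Section 2, text after Fig. 1.** The comprehensive assessment is said to include a "standardized diagnostic measure of the primary outcome (i.e. SM symptoms"). At T1, T2 and T3 parents and teachers are said to report the primary outcome only. In Table 2 the only symptom measures they complete at those times are SMQ-NL and SCS.
- **Sections 2 and 2.3.** The diary is completed by parents and by teachers, and the design has five phases, A to E.
- **Section 3.1.** The power statement concerns an effect from baseline to intervention by PDT, with individual p-values pooled to a group-level result.
- **Section 3.1.2.** For secondary outcomes the plan commits to "appropriate correction methods for multiple comparisons where relevant". Section 3.1.1 has no such statement.

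**The concern.** One of the study's aims is to examine the efficacy of the combined treatment. A reader who follows 3.1.1 would judge that aim on the diary; a reader who follows Table 2 would judge it on the questionnaires. Within the diary, the result could come from the parent or the teacher series, from any of several phase contrasts, and from either the PDT or Tau-U, since 3.1.1 says Tau-U can also be tested and pooled to a group effect.

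Section 3.1.2 recognises the risk of increased type I error but places the correction only on secondary outcomes. If results differ across informants, phases or instruments, the article does not settle which one is the primary finding, and the error rate attached to a positive primary conclusion is unknown.

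**Working it through.** **Step 1. What the article fixes and what it leaves open**

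| Element | Where | Status |
|---|---|---|
| Primary measure | 3.1.1 against Table 2 | ESM diary in one, SMQ-NL and SCS in the other |
| Informant | 2, 2.3 | Two; no lead informant and no combination rule |
| Contrast | 2, 3.1, 3.1.1 | Five phases; between phases in 3.1.1, baseline to intervention in 3.1; intervention covers B, C and D |
| Group-level route | 3.1, 3.1.1 | Pooled p-values, Tau-U, Friedman; not ranked |
| Correction | 3.1.2 | Secondary outcomes only |
| Per-test level, success rule | none | Not stated |

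**Step 2. The plan's own figures.** The article gives no error rate to reproduce. Its count of time points does reproduce: 3 per week × (2 + 25 + 12) weeks = 117, that is 6 at baseline, 75 in treatment and 36 in follow-up.

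**Step 3. Error if tests are independent.** Assume 0.05 per test and that any positive result counts as success. The chance of at least one false positive among m tests is 1 − 0.95^m.

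- One baseline-to-treatment contrast, two informants: m = 2, 1 − 0.95² = 0.098.
- The same plus one test each for SMQ and SCS: m = 4, 1 − 0.95⁴ = 0.185.
- Four adjacent contrasts (A-B, B-C, C-D, D-E), two informants: m = 8, 1 − 0.95⁸ = 0.337.

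**Step 4. Error allowing for dependence.** Contrasts share phases and the two informants describe the same child, so independence overstates the error. A null simulation (20,000 replicates) used 15 children, autocorrelation 0.4 (section 3.1) and phase lengths of 6, 25, 25, 25 and 36 points. The equal split of the 75 treatment points is an assumption. Each phase mean had variance (1 + 0.4)/(1 − 0.4)/n; each contrast was standardised, summed over children, divided by √15 and tested two-sided at 0.05.

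| Contrasts, both informants | Parent-teacher correlation 0 | 0.3 | 0.5 | 0.8 |
|---|---|---|---|---|
| A-B only | 0.101 | 0.095 | 0.090 | 0.077 |
| Each later phase against A | 0.205 | 0.208 | 0.192 | 0.166 |
| Four adjacent | 0.308 | 0.297 | 0.293 | 0.256 |
| All ten pairs | 0.475 | 0.461 | 0.446 | 0.390 |

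The simulation uses normal phase means in place of the PDT, so it shows the effect of multiplicity alone.

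**Step 5. Ranges.** One contrast with two informants gives about 8-10%. Adding the questionnaire tests gives at most 18.5% if they are independent. Adjacent contrasts give about 26% (simulated, correlation 0.8) to 34% (independent).

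**The case against.** The strongest reply is that the article does rank its measures. There is one primary construct, SM symptoms; section 2 says the diary is supplemented by the other assessments; and 3.1.1 makes the questionnaires validation. Table 2 has only T0 to T5 columns, where a diary kept three times a week fits poorly. Section 3.1 already points to one contrast and one pooled inference. The study describes its evidence as preliminary, and details such as the significance level and lead informant are commonly left to a full protocol or analysis plan.

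Much of this stands. The ranking in 3.1.1 softens the conflict, the omitted details are not in themselves a fault, and differences such as B-C or D-E are not evidence of efficacy against baseline.

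Three things remain. The layout argument fails, because Table 2 also lists the child well-being scale and the VFAS, which section 2.3.2 says are completed after each session. The contrast in 3.1 does not say which of the three treatment phases it covers. And the article does address multiplicity but commits to correction only for secondary outcomes.

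A reader might go further and infer that a false positive primary result is likely. The figures do not support that: no simulated scenario reaches one half. Treating all ten pairs and both informants as 20 independent tests gives 1 − 0.95²⁰ = 0.642, but pairs that share phases cannot be independent. Nor does the article say that any single instrument or contrast may carry the claim, or that there is no correction anywhere.

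**Conclusion.** The inconsistency is in the text and should be corrected. Section 3.1.1 and Table 2 name different primary measures, and 3.1.1 gives a group test under the primary heading to questionnaires it describes as validation. With two informants, several possible contrasts and correction stated only for secondary outcomes, the type I error of the primary conclusion is not controlled.

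The size depends on the reading. It is about 8-10% on the narrow reading closest to section 3.1, up to 18.5% if the questionnaire tests also count, and about 26-34% if all adjacent contrasts count. These figures rest on two assumptions the article does not state: 0.05 per test, and any positive result counting as success. The conclusion is inflation above the nominal level, not a probable false positive.

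**What to change.** 1. **Table 2.** Add the ESM diary, with parent and teacher as informants, as the primary measure. Relabel SMQ-NL and SCS as supportive (validation) measures, as 3.1.1 already describes them. Adjust the section 2 wording on T1 to T3 to match.
2. **Section 3.1.1, primary test.** Name one group-level test: the pooled PDT for the baseline-to-intervention contrast already used for power in section 3.1. State which treatment phase or phases it covers, which informant's series is used or how the two are combined, and the significance level.
3. **Section 3.1.1, everything else.** Treat the other informant's series, other phase pairs, Tau-U tests and the Friedman tests as supportive, and extend the correction in 3.1.2 to them (Holm or Benjamini-Hochberg).

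With one informant series or combined series, one contrast and one test, multiplicity no longer inflates the primary error above the chosen level. If both informants are kept as separate primary tests, a Bonferroni level of 0.05/2 = 0.025 each does the same.

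The cost is wording, settled before analysis, with no change to data collection or sample size. The downside is that fewer results can be presented as primary evidence.
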